### Randomisation and allocation concealment {16a} {16b}{16c}

Participants will be randomly allocated to intervention or control via block randomisation on a 1:1 ratio (control: intervention) using a computer-generated random number sequence created by an independent statistician. In addition, randomisation will be stratified by surgery type (i.e. ENT surgery, general surgery, neurosurgery, maxillofacial surgery, urology surgery, vascular surgery, orthopaedics, and other surgeries). Electronic allocation via an online platform (the REDCap™ randomisation module) will be used to conceal the treatment allocation from the researcher until they have been deemed eligible and screened.

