### Secondary outcomes

The secondary outcomes to be assessed include:Stress levels will be assessed via two methods:A)Saliva cortisol levels as measured by collecting 4–5 ml of saliva in a clean glass tube. The samples will be labelled with participant ID number and stored at −18°C until they are transferred to Saliva and Liquid Biopsy Translational Laboratory, Queensland University of Technology, for analysis using the Cortisol ELISA Assay Kit™ by an independent laboratory. The analysis results will be intended to determine the quantitative of cortisol by an enzyme immunoassay in human saliva. This is a highly sensitive test, with results changing in minutes after exposure to an anxiety-inducing or relaxing stimulus [26]. The sample will be used for the purposes of this research project only and will be destroyed at the end of this project.Saliva samples will be collected from participants by the Research Assistant at two-time points: on admission to the preoperative area (T1) and immediately before surgery (T2).B)Heart rate (HR) as measured manually for 1 min and the mean HR will be calculated. The Research Assistant will record HR at three time points: on admission to the preoperative area (T1), immediately before surgery (T2), and 1 h on arrival to the post-anaesthesia care unit (T3).Pain level as measured by the visual analogue scale for pain (VAS-P). The Research Assistant will ask the participants to rate their pain on the VAS-P tool at two time points: on admission to the preoperative area (T1) and 1 h on arrival to the post-anaesthesia care unit (T3).Patient satisfaction as measured by the Leiden Perioperative Patient Satisfaction questionnaire (LPPSq). The questionnaire is a valid and reliable tool used to assess and measure different aspects of patient satisfaction with perioperative care with 39 questions [36]. The participants will be asked to complete the questionnaire 24 h after surgery before discharge (T4).Hospital length of stay (LOS) as measured from the date of admission to discharge from hospital. The Research Assistant will collect this data from administrative records post-discharge.Adverse effects of the VR intervention at any time point as measured by the Virtual Reality Symptom Questionnaire (VRSQ). The questionnaire is a valid and reliable measure used to evaluate the possible occurrence of cybersickness symptoms, a type of motion sickness caused by exposure to VR [37]. The researcher will ask the participants in the intervention group to complete the questionnaire immediately before surgery (T2) (Fig. 3, Table 1).

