### Statistical plan {20a}

Characteristics of groups will be summarised using counts and percentages for categorical variables and means and standard deviations for continuous variables. The primary outcome (anxiety at Time 2 and Time 3 in stacked format) will be compared between groups at each follow-up time point using a linear mixed-effects regression model, with fixed effects including treatment arm time (categorical), the interaction between treatment and time, anxiety time point (either Time 2 or Time 3), surgical type (stratification variable), and the baseline value of the outcome variable. Differences in mean VAS-A scores between groups at each time point will be presented together with 95% confidence intervals and *p*-values. Continuous secondary outcomes with repeated measurements will be compared using the same model. Hospital length of stay will be compared using the rank-sum test. Patient satisfaction will be compared using an independent sample *t*-test and descriptive statistics will be used to summarise the VRSQ.

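### Length of stay and satisfaction are tested without surgery type, the randomisation stratum; the tests stay valid but lose power to the extent that surgery type predicts the outcome

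*Protocol article*

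**What the plan says.** The section on randomisation and allocation concealment uses 1:1 blocks and states that "randomisation will be stratified by surgery type". It names eight categories: ENT, general, neurosurgery, maxillofacial, urology, vascular, orthopaedics and other.

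The Statistical plan carries this factor into the primary mixed model, whose fixed effects include "surgical type (stratification variable), and the baseline value of the outcome variable". It extends the adjustment further: "Continuous secondary outcomes with repeated measurements will be compared using the same model".

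Two compared outcomes are treated differently in the same paragraph. For length of stay, "Hospital length of stay will be compared using the rank-sum test". For satisfaction, "Patient satisfaction will be compared using an independent sample" t-test. Nothing else in the article adds a stratified or adjusted analysis for either outcome. These are named tests, not details left open for a later analysis plan.

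**The concern.** Blocking within surgery type makes the arms nearly equal in surgical mix. An unstratified test does not know this. Its standard error allows for chance imbalance in surgery type that the design has largely removed, so p-values are too large on average. The stronger the link between surgery type and the outcome, the larger the excess.

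Length of stay is the outcome for which such a link is most plausible, because the strata run from ENT and maxillofacial surgery to vascular surgery and neurosurgery. Longer hospitalisation is also part of the rationale given in the Abstract and the Discussion. The loss is avoidable, and the paragraph is inconsistent with itself: the other between-group comparisons use the stratification factor and these two do not.

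**Working it through.** **Plan's own figure.** The article gives no power statement for either outcome. Its sample size of 150 (75 per group, 80% power, 5% type I error, 15% dropout) is for VAS-A only and enters here just as N.

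**Inputs from the article:** N = 150, 1:1 blocked allocation, eight strata.

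**Assumptions, because the article gives no values:** blocks of four; two-sided 5%; for length of stay, stratum sizes 10, 30, 15, 10, 20, 15, 35 and 15 (sum 150), lognormal stay rounded up to whole days, and a within-stratum log-SD of 0.6.

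**Step 1: expected size.** Let ρ be the share of outcome variance explained by surgery type. With strata balanced, the true variance of the arm difference is about (1 − ρ) times what the unadjusted test assumes. The actual size at nominal 5% is then about 2Φ(−1.96/√(1 − ρ)):

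- ρ = 0.10: 1.96/√0.90 = 2.07, size about 3.9%
- ρ = 0.25: 1.96/√0.75 = 2.26, size about 2.4%
- ρ = 0.41: 1.96/√0.59 = 2.55, size about 1.1%

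Incomplete blocks leave some imbalance, so simulated sizes should be at or somewhat above these.

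**Step 2: length of stay, simulated.** A log shift of −0.3 gives exp(−0.3) = 0.74, a 26% shorter stay. The share is ρ = b²/(b² + 0.6²), where b is the between-stratum log-SD; for example, 0.35²/(0.35² + 0.36) = 0.1225/0.4825 = 25%. Ranges show the spread over repeated runs of this scenario.

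| b | ρ | Rank-sum size | Rank-sum power | van Elteren power |
|---|---|---|---|---|
| 0 | 0% | 4.8–4.9% | 82–83% | 80–82% |
| 0.2 | 10% | 3.8–3.9% | 80–81% | 81% |
| 0.35 | 25% | 2.5–3.0% | 74% | 81–82% |
| 0.5 | 41% | 1.3–1.8% | 63–67% | 81–82% |
| 0.7 | 58% | 0.5–1.0% | 47–53% | 79–82% |

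The van Elteren test keeps its size near 5% throughout.

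**Step 3: a smaller effect.** A log shift of −0.1 gives exp(−0.1) = 0.905, about a 10% shorter stay. Rank-sum against van Elteren power is then 14 vs 16% at b = 0.2, 10 vs 15% at 0.35 and 9 vs 16% at 0.5. Across runs the range is about 8–15% against 15–17%.

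**Step 4: satisfaction, simulated.** Assumptions: a normal outcome, an effect of 0.5 total SD, 15% dropout and uneven strata. Total variance is held fixed, so the t-test's own power does not fall as ρ rises. The loss is the gap to the adjusted model.

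| ρ | t-test size | t-test power | Power, linear model with surgery type |
|---|---|---|---|
| 0% | 5.0% | 80.2% | 79.4% |
| 10% | 4.3% | 80.0% | 82.8% |
| 20% | 3.7% | 82.2% | 87.0% |
| 30% | 2.1% | 82.0% | 90.2% |

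Monte Carlo error in Step 4 is about 0.3 points for size and up to 1 point for power.

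**The case against.** The best defence is that the error is on the safe side. Neither test exceeds 5% type I error, both outcomes are secondary, and the trial is sized for VAS-A alone. All of this stands and limits the weight of the point.

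The 26% effect is also optimistic. The Background reports that earlier adult VR studies found no significant change in length of stay. At a 10% shorter stay, stratifying raises power only from low to slightly less low. This stands too: a reader might infer that the fix would make length of stay an adequately powered outcome, and it would not.

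A reader might also infer that both tests are conservative as a matter of fact. The document does not support that. It reports neither outcome by surgery type. At a 10% share the gain for length of stay is about one point, and with no link there is no conservatism. For satisfaction, nothing in the article suggests a strong dependence on surgery type.

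Finally, length of stay is defined as "Hospital length of stay (LOS) as measured from the date of admission to discharge from hospital", and one might infer that preoperative inpatient days dilute the comparison. The text gives this little support. The Screening section places screening on the day of surgery, Table 1 places it at hospital admission, and the Discussion refers to day-of-admission surgery. Together these point to same-day admission, so no change to the start date is warranted.

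None of this is a reason to leave the stratification factor out. Including it costs little in the worst case and gains materially if the link is moderate or strong.

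**Conclusion.** The point holds as a conditional loss of efficiency and an inconsistency within the Statistical plan. It is not a threat to validity. For length of stay, assuming a 26% shorter stay, the loss from ignoring strata is about 1 point of power at a 10% variance share, about 7 points at 25% and about 15–18 points at around 40%, with the size of the rank-sum test falling from about 4% to about 1.5%. For satisfaction, at an effect of 0.5 SD, the loss is about 3 points at a 10% share and 8 at 30%, and it may be close to nil. If surgery type has no effect, stratifying costs about 1–2 points.

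These sizes rest on assumed stratum sizes, block size, effect sizes and variance shares, none of which the article states. The direction does not: it follows from stratified blocking whenever surgery type predicts the outcome. The primary outcome and the repeated continuous secondary outcomes are unaffected.

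**What to change.** In the Statistical plan, replace the rank-sum test for length of stay with the van Elteren test (rank-sum stratified by surgery type). Because that test gives only a p-value, report an effect estimate with its confidence interval alongside, such as a stratified Hodges–Lehmann shift. Replace the t-test for satisfaction with a linear model on arm and surgery type. State a rule, fixed before unblinding, for pooling very small surgery-type strata, since eight strata share 150 participants. Leave the definition of length of stay as it is.

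The cost is a change of wording. Surgery type is already a randomisation variable and is listed under Other data, so no further participants, visits or data are needed. The downside is a power loss of about 1–2 points if surgery type turns out not to matter.

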#### Missing data {20c}

Missing data will be handled by complete case analysis. Data collection will occur within the same day and thus missing data should be rare.

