## Methods

### Study design and setting {8} {9}

A two-group parallel, single-centre, superiority, randomised controlled trial (RCT) with an allocation ratio of 1:1 will be conducted and reported in accordance with the CONSORT guidelines [27]. A total of 150 patients undergoing elective surgery will be randomised to the control (standard preoperative care) or intervention (standard preoperative care plus VR intervention) groups. The intervention will be delivered using the Oculus Quest 2 Virtual Reality Headset™ fitted with a smartphone (Fig. 1). This device has been chosen because it is the most advanced commercially available all-in-one VR device from Oculus, equipped with a highly immersive headset, two controllers, and integrated headphones. This study will be conducted in the surgical unit of a major Australian metropolitan hospital.

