### Criteria for discontinuing the trial in an individual {11b}

The researchers will monitor the participants continuously for side effects. If a side effect occurs, the VR session will be ceased immediately, and a treating medical team will be consulted. Also, there may be a risk of exacerbating the participant’s anxiety level associated with using a survey to assess anxiety. If this is the case, participants to be instructed to stop the survey and appropriate support will be provided by the researcher or medical team.

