### Sample size {14}

Based on the previous study by Bekelis et al. [24], a sample of 150 participants (75 per group) will provide 80% power to detect a 20% change on the 100-point VAS-A between groups with a type 1 error rate of 5%. This calculation assumes a dropout rate of 15%.

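### Complete case analysis fits badly with the stacked T2/T3 mixed model: read per participant it discards observed T2 scores, and its 'rare, same day' rationale is inconsistent with the 15% dropout allowance

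*Protocol article*

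**What the plan says.** All references are to the protocol article.

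- **Missing data {20c}** fixes the method: "Missing data will be handled by complete case analysis". The reason given is: "Data collection will occur within the same day and thus missing data should be rare".
- **Statistical plan {20a}** defines the primary outcome as "anxiety at Time 2 and Time 3 in stacked format". It is analysed by a linear mixed-effects model adjusted for the baseline value and surgery type, with a group difference reported at each time point.
- **Sample size {14}** says that "a sample of 150 participants (75 per group) will provide 80% power", and then: "This calculation assumes a dropout rate of 15" per cent.
- **Study design and setting {8} {9}** counts that number at allocation: "A total of 150 patients undergoing elective surgery will be randomised". The 15% is therefore an allowance for loss after randomisation.
- **Criteria for discontinuing the trial in an individual {11b}** provides that, if a survey worsens anxiety, "participants to be instructed to stop the survey and appropriate support will be provided".
- **Secondary outcomes** and **Table 1** place satisfaction at 24 h after surgery and length of stay after discharge.

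**The concern.** With T2 and T3 stacked, a mixed model fitted by likelihood uses a participant's T2 score even when T3 is missing, and is valid if missingness depends only on what has been observed. Complete case analysis, as the term is usually understood, removes the whole participant when any needed value is missing. Combining the two gives up the main advantage of the chosen model.

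Two things are at stake. The first is precision at T2, the assessment closest to the VR session. The second is bias: T3 follows surgery, so whether it is recorded is a post-randomisation event. If that event is related to T2 anxiety or to arm, deleting those participants also distorts the T2 comparison, for which the data were in hand.

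The justification is also weak on the document's own terms. It rests on missing data being rare, while the sample size section budgets for 15% loss.

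**Working it through.** **1. The plan's own figure.** The target is to "detect a 20% change on the 100-point VAS-A between groups with a type 1 error rate of 5" per cent. No SD is given, so 150 cannot be reproduced from the stated inputs. Solving backwards with a two-sided test (assumed) and SD 40 (assumed):

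- n per arm = 2 × (1.96 + 0.84)² × 40² / 20² = 62.8, so 63
- allowing for dropout: 63 / 0.85 = 74.1, so 75 per arm, 150 in total

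SDs of 20, 25, 30 and 35 give totals of 38, 60, 86 and 116. SD 40 is used below only because it matches 150.

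**2. Precision and power at T2.** 15% of 150 is 22.5 people, about 11 per arm. If all of them miss T3 only and are deleted whole:

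- SE with every T2 score: 40 × √(2/75) = 6.53
- SE after deletion: 40 × √(2/63.75) = 7.08
- ratio: 1/√0.85 = 1.085, about 8% larger, whatever the SD

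| T3 loss | T2 n per arm after deletion | Power at T2 |
|---|---|---|
| 0% | 75 | 86.5% |
| 2% | 73.5 | 85.8% |
| 5% | 71.25 | 84.7% |
| 10% | 67.5 | 82.8% |
| 15% | 63.75 | 80.6% |

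Power stays above 80% because the design already allows for this loss.

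**3. Bias, first set of assumptions.** 4000 simulated trials with 75 per arm, SD 40, T2–T3 correlation 0.5, a true effect of −20 at both times, and about 15% missing at T3 only.

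| Why T3 is missing | T2, complete cases | T2, all observed | T3, complete cases | T3, likelihood |
|---|---|---|---|---|
| Completely at random | −19.8 | −19.9 | −19.9 | −20.0 |
| Higher T2 anxiety, both arms | −18.1 | −19.9 | −18.9 | −19.8 |
| Higher T2 anxiety, VR arm only | −26.5 | −20.0 | −23.3 | −20.1 |

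**4. Bias, second set of assumptions.** T1 ~ N(60, 20); T2 = 20 + 0.6·T1 − 10·arm + N(0, 16); 75 per arm; 3000 trials; the T2 effect estimated by ANCOVA. The true effect is −10.

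| Why T3 is missing | T2 effect, complete cases |
|---|---|
| Higher T2 in controls only, 14% missing overall | −8.2 (SE 2.79, against 2.61 with all T2 data) |
| Higher T2 in VR arm only | −11.8 |
| Higher T2 in both arms, relative to each arm's own mean | −10.0 |
| Completely at random, 14% | −9.95 |
| Higher T2 in controls only, about 3% missing | −9.6 (SE 2.66 against 2.62) |

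An independent rerun of this second set gave the same pattern, within simulation error. Complete cases can understate or overstate the benefit, or be unbiased, depending on the mechanism. Using all observed data recovers the true value in every scenario examined, all of which are missing at random given T2 and arm.

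**5. The rationale against the schedule.** VAS-A at T1, T2 and T3 ends 1 h after arrival in the post-anaesthesia care unit, so same-day collection is accurate for the primary outcome. It is not accurate for satisfaction (24 h) or length of stay (after discharge).

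**The case against.** The strongest reply is that the article never says a participant loses T2. Data stacked by time point have one record per assessment, and complete case could mean only that missing records are not imputed, which would keep T2. That stands as a reading. It follows that the text allows two different primary analyses, so the sentence still needs settling.

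The 15% is a planning allowance, not a forecast, and cautious allowances are ordinary. That also stands: the two statements are inconsistent in tone and purpose but do not strictly contradict each other. At about 3% loss the effect on the estimate is small.

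A reader might infer from the stop-survey provision that the most anxious participants are the ones dropped. The document does not support this. The trigger is anxiety made worse by the survey, not a high score; no frequency is given; nothing says that data already collected are discarded; and the survey meant may include the APAIS screen, which precedes randomisation. It is a possible anxiety-related route to missing data and no more. If a survey is stopped at T2 itself, there is no T2 score to retain.

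A reader might also infer that the trial loses its planned power or that its effect is biased in a known direction. Neither follows. Power at T2 is 80.6% at the full 15% loss (SD 40 assumed), and the sign and size of any bias come from assumed scenarios.

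**Conclusion.** The point holds as a should-fix. A stated method (complete case analysis) is poorly matched to a stated model (stacked T2/T3 mixed model). Under participant-level deletion, which is the usual meaning but is not spelled out, observed T2 scores are wasted: the T2 standard error rises by about 8% at 15% T3 loss, and by little if loss is rare. The T2 and T3 estimates can be biased in either direction if missingness depends on T2 anxiety or arm. No passage establishes that it does, and the sizes shown rest on the assumed SDs, correlation and mechanisms.

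The same-day rationale is sound for T1 to T3, inapplicable to satisfaction and length of stay, and inconsistent with a 15% allowance for loss after randomisation.

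**What to change.** 1. Replace the complete case sentence with: *All randomised participants are analysed as allocated; every observed T2 and T3 value enters the mixed model by likelihood (REML) under missing at random, with no participant excluded for missing one time point.*
2. Limit the same-day statement to T1 to T3, and reconcile it with the 15% allowance, for example by saying that the 15% is a cautious planning margin.
3. Add one sensitivity analysis for departures from missing at random in VAS-A, such as shifting the missing values by a range of amounts.
4. Mean-impute a missing T1 VAS-A only if T1 is measured before allocation. Table 1 puts allocation at t0, ahead of t1, so the order must be reconciled first.

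The sample size does not change and the planned model already accommodates incomplete participants. The cost is a few sentences of text and one extra analysis.

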### Ethical issues {22}

The study, including the participant information and consent form, has been reviewed and approved by the Royal Brisbane & Women’s Hospital Human Research Ethics Committee (RBWH HREC) (HREC/2021/QRBW/74417). Participation is voluntary and decline to participate will involve no penalty or loss of benefits to which the participant is otherwise entitled, and participants may discontinue participation at any time without comment or penalty.

There are possible risks (side effects) associated with the VR intervention ^(38).^ Although rare, side effects may include headache, nausea, vomiting, sweating, fatigue, drowsiness, disorientation, and apathy [33]. Any adverse events that arise, whether related to the study intervention or not, will in the first instance be reported to the clinical nurse manager and to the researchers, who will then submit a report of the event to the HREC.

### Data storage, access, and disposal {19} {27}

Unique project codes will be assigned to participants on entry to the project and stored securely and separately from participant data. During each data collection, research staff will enter participant data into a database. At no time will identifiable study information be reported or made available to persons other than the research personnel.

All electronic data will be stored on a password-protected computer. All paper records will be kept in a locked cabinet in the Principal Investigator’s office. All data will be kept for 15 years following the project’s completion, after which time it will be destroyed or erased from the nominated drive. Only the study researchers will have access to any identifiable data, except where required by law. Data will be reviewed weekly by the researcher for auditing trial conduct.

If the participant decides to withdraw from the project, the researcher will discuss any special requirements linked to withdrawing.

